Audit data from screening practice is commonly used for determining program performance. However, audit data produces a single estimate of the recall/detection pair, and therefore has limited value for evaluating the tradeoff between recall and detection rates. To evaluate this tradeoff, a probability of malignancy (PoM) score is needed that can be compared to different thresholds for recall, but these are not obtained as part of screening practice. In essence, this PoM reflects the reader’s internal decision process, before applying a threshold to dichotomize their decision into a recall/no-recall outcome [4–6]. Laboratory studies allow for collection of PoM scores, which are then used to generate receiver operating characteristic (ROC) curves that quantify the tradeoff between sensitivity and specificity. ROC performance can be readily converted into estimates of recall and detection rates with knowledge of disease prevalence. However, these studies are potentially subject to so-called *laboratory effects* that may lead to biased results. Typically, laboratory studies involve the enrichment of the testing set with additional examples of positive cases, which can also lead to prevalence biases in reader responses [7].

The ROCS trial avoids the potential issue of laboratory effects and the difficulty of extrapolating current performance into predictions of performance at different operating points by using a novel system to acquire PoM scores during actual screening practice. The system is designed to minimally interrupt clinical workflow, and to automatically associate the PoM response with the case identifier. In this Special Report, we present the design of the ROCS trial, aimed at determining the performance tradeoffs for digital mammography interpretation in the actual breast cancer screening environment of the Dutch National Breast Cancer Screening Program. At present, the first stage of data acquisition, the accrual of reader case scores during screening is completed, and the results of this stage are presented. The second and final stages of data acquisition, involving the determination of the ground truth for the recalled cases and, then, after the 2-year waiting period, for the non-recalled cases, are ongoing.

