### Overall study design

The primary aim of the ROCS trial is to estimate the trade-off between recall rate (RR) and cancer detection rate (CDR) by estimating the RR-CDR curve for the average radiologist in the Dutch National Breast Cancer Screening Program directly from screening interpretations. Secondary endpoints include estimating the ROC curve for the average breast radiologist during actual screening interpretation and determining if reader performance changes as they progress within one reading session, as previously reported [8].

For this, ROCS involves obtaining a PoM rating from screening radiologists (*n* = 20) for each and every case (*n* = 2,000 per radiologist) they interpret during several screening reading sessions (approximately *n* = 8), with minimal interruption or diversion from their usual reading workflow. The outcomes of the cases included in the ROCS trial will be obtained from short-term (1 year) follow-up of the recalled cases via the screening organization and long-term (2 years) follow-up via the Netherlands Cancer Registry.

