### Study cases

The digital mammography cases included in ROCS involved cases acquired and interpreted as part of the Dutch National Breast Cancer Screening Program. In the Netherlands, the screening program invites all women between the ages of 50 and 75 to be screened for breast cancer with digital mammography nominally every 2 years, with this period having some regional variability. All image acquisitions, involving the standard cranio-caudal (CC) and medio-lateral oblique (MLO) views, are performed at dedicated screening centers equipped with the same imaging systems (Selenia, Hologic Inc.). The systems are all under the same quality control protocol, performed by the same group of physicists at the Dutch Expert Centre for Screening (LRCB) for the nationwide program. The technologists that acquire all images are specifically trained and undergo regular refresher education and auditing on screening mammography. Cases are interpreted in batches, at dedicated reading centers, usually within 1 or 2 days of acquisition. All reading is performed by certified screening radiologists, who undergo additional periodic training and evaluation to be a part of the screening program. Throughout the program, the mammograms are viewed on a SecurView mammography screening workstation (Hologic Inc.) with dual-head 5-megapixel monitors (Coronis 5MP Mammo, MFGD 5621 HD, Barco). The mammography monitors used are also tested by the physicists of the LRCB, as per established protocols.

Although the Dutch National Breast Cancer Screening Program involves independent double reading of all cases with consensus or arbitration for disparate decisions, ROCS is focused on individual reader performance. This is because the overall aim of this endeavor is to gather the evidence needed to inform the setting of new performance guidelines for radiologists. Therefore, all performance estimates are performed at the level of individual readers, and then these are aggregated into results for the screening program as a whole. In addition, due to the nature of screening, all acquisition and analysis are performed at the per case level, as opposed to per breast or per lesion.

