### Study radiologists

All radiologists participating in the Dutch National Breast Cancer Screening Program were considered eligible, since they already have to meet minimum training, continuing certification, and case volume requirements (*n* > 3,000 screens per year) to participate in the program. To maximize the diversity in geographic, socio-economic, and other factors in the screening cases, radiologists from five different reading centers around the country were targeted to participate in ROCS. In total 21 radiologists were recruited to participate in the study, since we aimed to recruit at least 20 radiologists.

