### Study endpoints

The primary endpoint of ROCS is the estimation of the curve describing the relationship between recall rate and cancer detection rate for the average reader in the Dutch National Breast Cancer Screening Program. From this curve, it would be possible to determine the benefit, or lack thereof, in increased number of cancers detected at screening due to an increase in the recall rate. In addition to the PoM ratings from the exam interpretations, constructing this curve involves obtaining the outcome of the cases recommended for recall by each participating radiologist. This data is available through the screening organization. As per the programmatic definition, breast cancer diagnosed within 12 months of the woman being recalled from screening is defined as a screening-detected cancer.

As related secondary endpoints of the ROCS trial, two different average-reader ROC curves will be estimated to better characterize performance of readers in the screening program. The first will be constructed considering all cancers as defined by the program, i.e., all breast cancers diagnosed within 24 months after the date of screening acquisition. Interval cancer cases will be identified through linkage with the Netherlands Cancer Registry after the necessary waiting period. However, it is known that approximately half of all interval cancers are visible at the prior screening [10]. To identify these, all interval cancer cases will be reviewed by a panel of experts and graded as the cancers being *not visible*, *present with minimal signs*, or as *missed*. This is a common procedure in the Dutch National Breast Cancer Screening Program, performed for education and quality assurance purposes. Additional ROC curves will be constructed, one excluding interval cancers deemed *not visible* and one involving only invasive cancers.

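### The fixed 24-month cancer window for the secondary ROC curves can count cancers found at an early next screening round as positives the index reader missed

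*Protocol article*

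**What the plan says.** In the protocol article, *Study endpoints* describes the first average-reader ROC curve thus: "The first will be constructed considering all cancers as defined by the program", which it spells out as "all breast cancers diagnosed within 24 months after the date of screening acquisition". The clock starts at image acquisition and runs for the same time for every woman. *Overall study design* matches this with "long-term (2 years) follow-up via the Netherlands Cancer Registry", and the *Introduction* speaks of establishing truth "after the 2-year waiting period, for the non-recalled cases".

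*Study cases* describes the screening interval as "nominally every 2 years, with this period having some regional variability". *Study radiologists* says that, to widen geographic and other diversity, "radiologists from five different reading centers around the country were targeted to participate in ROCS".

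On ascertainment, *Study endpoints* says "Interval cancer cases will be identified through linkage with the Netherlands Cancer Registry after the necessary waiting period", and that "all interval cancer cases will be reviewed by a panel of experts". Further ROC curves leave out interval cancers that the panel could not see at the index screen, or keep invasive cancers only. The article does not define an interval cancer relative to the next screen. It also does not say how a cancer found at a next-round screen before 24 months is classed.

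**The concern.** The window is as long as the nominal screening interval, so it has no margin. Where the next round comes early enough for work-up to finish inside 24 months, the literal rule takes in cancers found by that next screen. The woman was not recalled at the index screen, so her index score will usually be low and the cancer will look like a miss. Whether it counts depends on when she was re-invited and not on how the index mammogram was read.

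The planned safeguards do not clearly catch this. A cancer found at the next screening round is not ordinarily called an interval cancer. It may therefore bypass the panel and remain in the curve that drops non-visible interval cancers. If invasive, it also remains in the invasive-only curve.

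The ROC curves are secondary, but they have a use. *Data analysis* allows the optimal operating point to be sought on either type of curve, the *Discussion* would choose the programme's operating point from one or both, and the *Abstract* offers the data as a benchmark for new technologies.

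**Working it through.** The article gives no figure for the effect of the window, so there is none to reproduce. The base does agree: 20 readers × 2,000 cases = 40,000, as in *Study cases*.

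**Inputs from the article.** N = 40,000. Detection rate (CDR) = 5.53/1000 (nominal value in the sample-size model) or 6.7/1000 (programme, 2018). Each is used throughout its own calculation, and the two are not mixed.

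**Assumptions, not in the article.**
- f is the share of women whose next-round cancers would be diagnosed before 24 months.
- Interval cancers number 1, 2 or 3 per 1000 over two years, spread evenly in time.
- The next-round detection rate equals the current one, with full attendance.
- The CDR stands for the index reader's detected cancers.

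**Early returns.**

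Added positives = f × N × CDR. At f = 10%: 0.10 × 40,000 × 5.53/1000 = 22.1, or 0.10 × 40,000 × 6.7/1000 = 26.8. The screen-detected cancers number 221.2 or 268.

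Apparent sensitivity = screen-detected ÷ (screen-detected + interval + added).

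| CDR per 1000 | Interval cancers per 1000 | f = 0 | f = 10% | Fall (points) |
|---|---|---|---|---|
| 5.53 | 1 | 221.2/261.2 = 0.847 | 221.2/283.3 = 0.781 | 6.6 |
| 5.53 | 2 | 221.2/301.2 = 0.734 | 221.2/323.3 = 0.684 | 5.0 |
| 5.53 | 3 | 221.2/341.2 = 0.648 | 221.2/363.3 = 0.609 | 3.9 |
| 6.7 | 1 | 268/308 = 0.870 | 268/334.8 = 0.800 | 7.0 |
| 6.7 | 2 | 268/348 = 0.770 | 268/374.8 = 0.715 | 5.5 |
| 6.7 | 3 | 268/388 = 0.691 | 268/414.8 = 0.646 | 4.5 |

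At f = 5% the added positives are 11 to 13 and the fall is about 2 to 4 points. At f = 25% they are 55 to 67 and the fall is about 9 to 16 points. At f = 0 nothing changes.

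**Late returns.**

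Interval cancers after 24 months but before the next screen = share × N × (two-year interval rate ÷ 2) × months late ÷ 12.

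With 10% of women 3 months late and 2 per 1000: 0.10 × 40,000 × 1/1000 × 3/12 = 1.0 case. Over 1 to 3 per 1000 the range is 0.5 to 1.5 cases. With CDR 6.7, sensitivity would move from 0.8701 to 0.8687, 0.7701 to 0.7679, or 0.6907 to 0.6881 if these cases were included, which is about 0.1 to 0.3 points. Only with half of all women 6 months late does this reach 5 to 15 cases and 1.4 to 2.6 points.

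**The case against.** The strongest reply is that nothing in the article shows that any woman in the five centres returned before 24 months. *Study cases* gives neither the size nor the direction of the variability. If all of it runs towards longer intervals, the early-return effect vanishes. This stands, and it makes the bias conditional.

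The window is also declared to be the programme's own definition, and a fixed window follows every woman equally. That explains the choice and makes it a reasonable sensitivity analysis. It does not make an audit rule suitable as the truth for a reader's ROC curve. A cancer found by screening shortly before 24 months may, however, have been visible at the index exam, so not all such cancers would be false misses. This also stands.

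The full protocol may define interval cancers so that early next-round cancers reach the panel. In that case the curve without non-visible cancers would remove some of them, but the first curve, as literally defined, would still contain them all.

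A reader might go further and infer that cancers are in fact misclassified in both directions across regions, and that differences between readers or centres will partly reflect invitation timing. The article does not support this. It does not describe the interval distribution, late losses are small for modest delays, and the planned curves are for the average reader. No comparison of ROC performance between readers or centres is stated.

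**Conclusion.** The point holds as a conditional weakness of a stated rule. The article fixes a 24-month truth window without regard to mode of detection, says that the interval varies by region, and does not reconcile the two. Each 10% of women whose next-round cancers are diagnosed inside the window would cost about 4 to 7 points of apparent sensitivity at the current threshold. This rests on the assumed interval cancer rates of 1 to 3 per 1000, full attendance and an unchanged detection rate. The effect on the area under the curve was not computed.

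It would be wrong to read this as a threat to the main result. The primary recall-detection curve counts cancers diagnosed within 12 months of recall and does not use the 24-month window. The change is worth making because it is cheap and the affected curves may inform the choice of operating point.

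**What to change.** For the ROC curves, end each woman's window at her next screening exam or at 24 months, whichever comes first. State that cancers detected at the next round are not index positives, and whether those women enter as negatives or are left out. At 27 in 40,000 (0.07%), that choice barely moves specificity. Report their number separately by centre, with the distribution of screening intervals, so that the reader can see whether f is zero or material. Keep the fixed 24-month programme definition as a sensitivity analysis.

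The cost is one extra date per woman, the next screening exam, which the screening organization should be able to supply as it already provides outcome data. Follow-up becomes slightly unequal between regions, and some next-round cancers that were visible at the index exam leave the main ROC truth set. The separate count and the sensitivity analysis show how much this matters. The change does not recover interval cancers after 24 months, a loss that is small unless delays are long and common.

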### Description of the model for determining sample size

A model of breast-cancer screening was derived and used to evaluate the number of radiologists and screening exams that would generate a RR-CDR difference curve of sufficient precision. The model is only briefly described here, but see the accompanying online supplement for a thorough description of the parametric form of the model, the data used to fit the model parameters, and the model manipulation used to generate a RR-CDR difference curve. Conceptually, this curve is generated by changing the PoM score used as the threshold for recall and comparing the RR and CDR to the nominal values using a PoM threshold of 0, which represents screening as it is currently practiced. Changing the PoM threshold allows us to predict the effect of a change in RR on CDR, and to predict the precision of the difference estimates for specified numbers of readers and cases. The values for the model parameters were estimated using data from the Dutch National Breast Cancer Screening Program during the period from 2010 to 2015.

Using this model, Fig. 2 shows the CDR prediction and the resulting uncertainty of the estimates based on acquiring data from 20 radiologists, each reading 2,000 screening exams. As described above, this represented a large but feasible study that could be completed in a reasonable time period, and so we assessed the adequacy of this sample size. The figure assumes that the recall rate is “induced” by adjusting the PoM threshold for recall to achieve a fixed reduction in recall rate (e.g., reduce recall by 0.5%). The resulting curve is given in terms of differences with the nominal rates (RR = 2.37%, CDR = 5.53/1000) with error bars representing the expected 95% confidence interval of these differences. For changes in the recall rate of up to 1%, the standard deviation of the CDR difference is 0.12/1000 or less. This level of precision in the difference justified commencing the study.

**Fig. 2 Fig2:**
[figure not shown]
Model-based estimates of cancer-detection rate changes as a function of recall-rate changes induced by changing the PoM threshold used for recall. The error bars show the expected 95% confidence interval from precision estimates across the 20 simulated readers (see online supplement).

### Data analysis

The PoM ratings for each radiologist will be used to construct recall and detection rate curves similar to those shown in Fig. 2, as well as traditional ROC curves, using well-established software for this task [11–15]. The radiologist-specific curves can then be averaged into a curve representing estimated group performance across different thresholds for recall. In addition to the visual presentation of the curves, utility analysis can be used as a rigorous approach to determining the optimal operating point on the ROC or recall/detection rate curves [16–19].

## Results

To date, the data acquisition at the reading centers has been completed. In total, 21 screening radiologists from five screening centers participated in the study between 19 March 2019 and 6 June 2019, resulting in the acquisition of a total of 42,215 recorded radiologist PoM scores and timestamps. The average number of records per radiologist was 2,010 entries (range: 954–2,842), with 14 radiologists recording more than 2,000 cases. The completion date for each radiologist varied, depending on their reading volume during the study period. In addition, the final total number of cases scored by each radiologist varied, since whole sessions were recorded, instead of data accrual stopping mid-session if 2,000 cases were reached.

The distribution of the recorded scores is shown in Fig. 3. An adequate distribution across the entire available scoring range was obtained, which is crucial to be able to construct adequate recall/detection rate and ROC curves. It should be noted that the number and distribution of scores shown here are based on the entirety of the records obtained. Therefore, it is expected that a small percentage of all the obtained records will have to be excluded from the final analysis due to a number of different issues, such as inability to obtain the final outcome for cases, among other issues.

**Fig. 3 Fig3:**
[figure not shown]
Distribution of the case scores for all 42,215 records obtained during the ROCS trial. Note that the *y* axis is plotted in logarithmic scale. The plot shows that an adequate distribution of scores was obtained across the entire available scoring range, and hence the potential problem of having all scores being clustered at the two ends, at −100 and +100, was avoided

The final results of the trial will be available once the short- and long-term waiting periods for collection of the actual outcomes are known.

## Discussion

The ROCS data acquisition approach acquires PoM scores and timestamps from radiologists in actual practice as they read screening mammograms. The use of external hardware, in this case a tablet and a webcam, allows for recording this data without having to modify protected and often proprietary workstation software to record a rating and timestamp per case. A simple GUI that only involves swiping on a touchscreen to enter the response, with automatic assignment of a timestamp, results in minimal intrusion of the workflow. A photographic confirmation of the case identifier avoids the need for the reader to confirm the entry or to manually move to the next case, further minimizing the disruption of the workflow. The participating radiologists reported that the procedure was not intrusive to their work.

The ROCS data collection procedure is well suited for high-volume image interpretation studies. In national screening programs, as in the Netherlands, this makes feasible the collection of such data from multiple sites for comparison. The flexibility of locating and aiming the webcam at any area of a computer monitor should allow for a similar setup even in more heterogeneous reading environments. Given that the rest of the data collection procedure is independent of the review workstation setup, the approach used in the Netherlands should be feasible for similar studies based on case ratings acquired during practice. As a result of this study, it will be possible to evaluate the tradeoff between recall rate and cancer detection rate, based on actual screening data, avoiding, or at least minimizing, any “laboratory” effect [7].

One alternative to this approach would be to construct a curve from a plot of RR/CDR pairs collected from an international group of screening programs. Since different programs operate with differing recall rates, this would give some indication of the tradeoff between recall and detection rates. However, it has been shown that there is no association between recall and detection rate internationally [20], although such association can exist within one program [21]. A variety of factors, such as screening interval, cultural differences, diagnostic infrastructure, and the medico-legal environment, impact recall and cancer-detection rates for a program, region, or country. This makes estimation of a RR/CDR curve from international data problematic.

Once such an RR-CDR and/or ROC curve is constructed, then the optimal operating point for the program can be selected based on outcomes in a data-driven manner. Knowledge of the optimal operating point could then be used to develop guidance for radiologists regarding their recall rates. This process assumes that radiologists are willing to implement these recommendations. But the change in recall rates after the recommendations derived from the Otten et al study supports the idea that Dutch radiologists are capable of adjusting their performance in response to screening program priorities. In addition, the Netherlands is evaluating the possibility of a transition to digital breast tomosynthesis and/or incorporation of artificial intelligence–based approaches for breast-cancer screening, as in other countries throughout the world. Therefore, in the future there will likely be a need to re-evaluate the trade-off between cancer detection and recall rate for new screening methodologies. If so, it would be ideal to undertake that evaluation having a clear understanding of this same trade-off in the current implementation of breast-cancer screening.

